## Abstract

**Background:**

Rectal cancer is a common cancer worldwide. Surgery for rectal cancer with low anterior resection often includes the formation of a temporary protective loop ileostomy. The temporary ostomy is later reversed in a separate operation.

One complication following stoma closure is the development of a hernia at the former stoma site, and this has been reported in 7–15% of patients. The best method to avoid hernia after stoma closure is unclear. The most common closure is by suturing only, but different forms of mesh have been tried. Biological mesh has in a randomized trial halved hernia incidence after stoma reversal. Biosynthetic mesh and retromuscular mesh are currently being evaluated in ongoing studies.

**Methods:**

The present multicenter, double-blinded, randomized, controlled study will compare standard suture closure of the abdominal wall in loop ileostomy reversal with retromuscular synthetic mesh at the stoma site. The study has been approved by the Regional Ethical Review board in Stockholm.

Patients aged 18–90 years, operated on with low anterior resection and a protective loop ileostomy for rectal cancer and planned for ileostomy reversal, will be considered for inclusion in the study. Randomization will be 1:1 on the operation day with concealed envelopes. The estimated sample size is intended to evaluate the superiority of the experimental arm and to detect a reduction of hernia occurrence from 12 to 3%. The operation method is blinded to the patients and in the chart and for the observer at the 30-day follow-up. The main outcome is hernia occurrence at the stoma site within 3 years postoperatively, diagnosed through CT with strain. Secondary outcomes are operation time, length of hospital stay, pain, and 30-day complications.

**Discussion:**

This double-blinded randomized controlled superiority study will compare retromuscular synthetic mesh during the closure of loop ileostomy to standard care. If this study can show a lower frequency of hernia with the use of prophylactic mesh, it may lead to new surgical guidelines during stoma closure.

**Trial registration:**

ClinicalTrials.gov NCT03720262. Registered on October 25, 2018.

**Supplementary Information:**

The online version contains supplementary material available at 10.1186/s13063-023-07430-w.

## Ethics and dissemination

The study has been approved by the Regional Ethical Review board in Stockholm (protocol no: 2017/1693-31/2), with amendment nos.: 2021-00818, 2019-01860 and 2022-05253-02. The results will be disseminated through conventional scientific channels.

## Strengths and limitations of this study

This is to our knowledge the only randomized controlled study to investigate synthetic mesh to prevent hernia after loop ileostomy closure.The primary outcome of hernia will be measured objectively and is clinically relevant and important to patient and physician alike.The trial is double-blind.The planned sample size is adequate to evaluate the superiority of the intervention arm.

## Introduction

### Background and rationale

Rectal cancer is a common form of cancer worldwide, with an age-standardized incidence rate of 14.4–16.6 per 100,000 for men in Europe, Eastern Asia, and Australia [1]. A temporary protective loop ileostomy is widely used when operating rectal cancer with low anterior resection [2–5]. The purpose of this practice is to reduce the impact of possible anastomotic leakage, but the method is constantly under debate because of its complications [6]. Ostomies can reduce the quality of life by causing leakage, parastomal hernia, and prolapse [7–11].

A temporary ostomy is reversed in a separate operation. One complication in connection with stoma closure is the development of a hernia at the former stoma site. A hernia is a weakening of the layers of the abdominal wall [12], which may cause pain and discomfort, but also more serious complications such as obstructed or strangulated bowel. The incidence of hernia after ostomy closure varies between 7 and 35% [13–20], whilst in studies including only ileostomy reversal, the hernia incidence was 7–15% [16, 17, 19–21].

The best method to avoid hernia after stoma closure is unknown. Most commonly, surgeons close the aponeurosis in one layer with a monofilament suture [20]. The use of prophylactic mesh in the abdominal wall has been tried in smaller non-randomized studies [22–24]. A meta-analysis from 2021 including both ileo- and colostomies showed a reduction in hernia incidence from 18.1 to 7.8% with no increase in complications using different types of reinforcing mesh [25]. In a retrospective study from 2018, the use of synthetic mesh reduced the incidence of hernia from 17.2 to 1% [24].

In a retrospective comparative study reviewing only the closure of ileostomies, the hernia incidence was reduced from 36.1 to 6.4% with a synthetic onlay mesh [26]. A multicenter study, randomizing loop ileostomy reversal between biological mesh and standard closure, showed significantly lower proportions of stoma site hernia, 12% vs 20%, in the mesh group, without increasing the complication rate [27].

The use of synthetic mesh is a well-established method in hernia repair, but there are no guidelines for abdominal wall closure in stoma reversal, despite the large defect in the aponeurosis. The ongoing PRINCESS study evaluates biosynthetic mesh for loop ileostomy reversal [28]. No completed randomized studies have compared a synthetic mesh with standard closure, but the ongoing study PELION are planning to evaluate synthetic mesh for loop ileostomy closure [29]. If the present study can detect a decreased frequency of hernia occurrence when using prophylactic mesh, it may lead to new recommendations for this patient group.

## Objectives

We hypothesize that a synthetic mesh placed retromuscularly in the abdominal wall reduces the frequency of hernia at the stoma site without increasing the risks of infection or other complications.The primary objective is to study whether a retromuscular synthetic mesh at the stoma site gives fewer hernias at the stoma site compared to a standard closure.The secondary objective is to compare operation time, length of hospital stay, pain, and 30-day complications, between the two groups.

## Trial design

Prevention of hernia after loop ileostomy reversal (PHaLIR) is a non-commercial clinical trial with the purpose of finding an operating method that reduces the incidence of hernias without increasing complications in patients undergoing loop ileostomy closure.

PHaLIR is a prospective, parallel-group, double-blinded randomized study in which patients planned for stoma reversal after rectal cancer surgery will be randomly allocated to an intervention group (retromuscular mesh repair (Ultrapro Advanced™, Ethicon, Hamburg, Germany)) or the control group (sutured abdominal wall closure). The allocation ratio is 1:1. The groups are parallel and non-crossover and the framework in the primary objective is superiority.

### Eligibility criteria

All patients from the included centers who fulfill the inclusion criteria are to be evaluated for participation in the study. Patients not included in the study will be registered in the screening log with reason for non-participation.

#### Inclusion criteria

Patients undergoing low anterior resection for rectal cancer with a diverting loop ileostomy and planned for stoma reversal with suture of the aponeurosis according to standard routines.Age 18–90 years

#### Exclusion criteria

Language barrier or cognitive disabilityRecurrent inoperable cancer (patients with operable metastasis are not excluded)Large parastomal hernia not suitable for standard closure

#### Trial center requirement

Eligibility criteria for surgeons are that at least one should be a specialist with experience of colorectal surgery.

Centers can participate provided that the center has one local investigator in charge and that loop ileostomy reversals after low anterior resection for rectal cancer are performed in the center. Where stoma reversal and rectal cancer surgery are performed in different hospitals, the center where stoma reversal is performed will be responsible for the randomization, operation, and 30-day visit, whereafter the primary referral center will be responsible for a 1 and a 3-year follow-up.

### Who will take informed consent?

The patients will be identified and asked about participation when they come for postoperative follow-up after rectal cancer surgery and will be planned for ileostomy reversal. Potential study participants will be given oral and written information by the responsible surgeon. Signed informed consent is required from all study participants.

### Additional consent provisions for collection and use of participant data and biological specimens

The study does not collect biological specimens and does not have any associated ancillary studies.

### Interventions

#### Explanation for the choice of comparators

Reversal of loop ileostomy is a common surgical procedure in colorectal departments. Standard treatment entails closure of the abdominal wall with PDS 2/0 monofilament in one layer.

#### Surgical methods

##### Preoperative measures

One dose of preoperative oral antibiotic is to be given in the morning of the operation day. The antibiotics used will be sulfametoxazol/trimetoprim 800 mg/160 mg 1 tablet, and Metronidazole 400 mg, 3 tablets. Antithrombotic prophylaxis should be given according to local routines. Enhanced recovery programs may be used wholly or partially, but the program chosen by a clinic should not change during the study period.

##### Operation description

On the day of surgery, the patient will be randomized to standard abdominal wall closure according to the surgeon’s preference; this in most cases will be closure with 2/0 absorbable monofilament in one layer, or placement of retromuscular mesh, Ultrapro-Advanced™, size 5 × 5 cm. The operation method in the intervention arm will be as follows:A circular incision will be made around the stoma.The stoma will be detached from the abdominal wall. A hand-sewn anastomosis using 4/0 absorbable monofilament in one layer, with seromuscular suture, will be performed.The bowel will be reinserted in the abdominal cavity.The posterior rectus aponeurosis (or the peritoneum depending on the placement of the stoma) will be mobilized from the surrounding tissue and sutured with a 2/0 slowly absorbable monofilament running suture with a start and a stop knot.The 5 × 5 cm Utrapro Advanced mesh will be placed in the retromuscular space. It should fill the width of the sheath of the rectus muscle.A widening of the incision crosswise will be permitted if there are technical difficulties.The anterior rectus sheath will be closed with a 2/0 non-absorbable monofilament running suture with a start and a stop knot.The skin will be closed with an intracutaneous purse-string suture using 3/0 or 2/0 non-absorbable monofilament. If the incision is extended, the extension will be closed with a 4/0 absorbable monofilament running intracutaneous suture prior to the purse-string suture.Finally, 20 ml Marcain/adrenalin 5 mg/ml 20 will be injected.

#### Adherence assessment

No specific adherence assessment is planned.

#### Criteria for discontinuing or modifying allocated interventions

The following situations resulting in discontinuation may arise:A patient may have been inadequately enrolled, not meeting the eligibility criteria. This patient should be excluded from data analysis and only reported in the flow chart.If a patient dies or is lost to follow-up, the data can be used until the date of the last follow-up.If a patient withdraws from the study, the study data collected until this point will be used.

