### Randomization

The randomization envelopes will be stored with the operation protocol and the instructions for the operation in a place convenient for each center. The envelope will be opened by the surgeon performing the operation on the operation day, before starting the operation.

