**Table Tabb:** 

• Age	operation protocol, surgeon
• Gender	operation protocol, surgeon
• Length	operation protocol, surgeon or anesthetist nurse
• Weight	operation protocol, surgeon or anesthetist nurse
• ASA class	operation protocol, surgeon or anesthetist nurse
• Smoking	operation protocol, surgeon
• Immunosuppression	operation protocol, surgeon
• Diabetes	operation protocol, surgeon
• Collagenous disease	operation protocol, surgeon
• Parastomal hernia preop	operation protocol, surgeon
• Operating time	operation protocol, surgeon
• Time for abdominal wall closure	operation protocol, surgeon
• Bleeding	operation protocol, surgeon or anesthetist nurse
• Bowel injury	operation protocol, surgeon
• Complication	30-days follow up, doctor
• SSI	30-days follow-up, doctor
• Postop hernia	30-day follow-up, doctor, 1 year, 3 years, CT
• Pain and inconvenience	patient, nurse, doctor on follow-up, questionnaires

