## Statistical methods

### Statistical methods for primary and secondary outcomes

Baseline characteristics between the intervention and non-intervention groups will be compared with paired tests. The incidence of hernia at the stoma site at 1 and 3 years will be compared between the two groups with paired tests and in a Kaplan-Meier model. Hernia in the abdominal wall is defined according to Muysoms [12].

If there are any imbalances between the two groups regarding factors known to influence the risk of hernia (e.g., sex and BMI), adjustment with regression analysis will be done. All data will be analyzed according to the intention-to-treat principle, as well as a per protocol analysis. Secondary outcomes will be compared between the groups by paired tests.

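### Patients found ineligible are dropped from all analysis, with no limit to the time before randomisation, which contradicts the stated intention-to-treat analysis

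*Protocol article*

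**What the plan says.** The protocol article's section on criteria for discontinuing or modifying allocated interventions lists this situation first: "A patient may have been inadequately enrolled, not meeting the eligibility criteria". Its instruction is: "This patient should be excluded from data analysis and only reported in the flow chart". In the same section, patients who die, are lost or withdraw keep the data collected up to that point. Only the ineligible lose all of theirs.

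The statistical methods section says: "All data will be analyzed according to the intention-to-treat principle, as well as a per protocol analysis". It makes no exception for ineligible patients.

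Three other places bear on the point:

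- **Randomization:** "The envelope will be opened by the surgeon performing the operation on the operation day, before starting the operation".
- **Exclusion criteria:** "Large parastomal hernia not suitable for standard closure". The other exclusions are language barrier or cognitive disability, and recurrent inoperable cancer.
- **Data collection table and Implementation:** the item "Parastomal hernia preop" is recorded by the surgeon on the operation protocol, which is completed after surgery.

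**The concern.** A randomised patient cannot both stay in an intention-to-treat analysis and be removed from all analysis. The article already plans a per-protocol analysis, where such exclusions could sit, but the exclusion rule is not confined to it. Two analysts following the text could build different primary analysis sets.

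Removing randomised patients as ineligible can be defended if two conditions hold: eligibility rests on facts fixed before randomisation, and the decision is made blind to arm. The article states neither. The person best placed to notice an unsuitable abdominal wall at operation already knows the arm, and the criterion is worded in terms of the control technique. A doubtful wall could be called unsuitable more readily when standard closure has been assigned. That would remove high-risk patients from the suture arm and hide part of a mesh benefit.

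**Working it through.** **1. The two rules side by side.** For a patient found ineligible before randomisation, the rules do not conflict, because intention-to-treat concerns randomised patients. For a patient found ineligible after randomisation, the discontinuation section says to remove and the statistical section says to keep. Enrolment is suggested at the 30-day visit after cancer surgery and randomisation is on the day of reversal, so both cases can occur. The rule does not separate them, and its heading refers to allocated interventions.

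**2. Expected events.** Inputs from the sample size section: 104 per arm, 12% v 3%.

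- Suture: 104 × 0.12 = 12.48
- Mesh: 104 × 0.03 = 3.12
- Total: 15.6, about 16 hernias

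The 104 is used here only as the stated arm size. The two-sided formula n = [z₀.₉₇₅√(2p̄q̄) + z₀.₈√(p₁q₁+p₂q₂)]² / (p₁−p₂)², with p̄ = 0.075, gives (1.960 × 0.3725 + 0.842 × 0.3670)² / 0.0081, or 134 per arm. A one-sided test (1.645 in place of 1.960) gives 105. That mismatch is a separate matter and this point does not depend on it.

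**3. How far a few exclusions can move a result.** Fisher's exact test is used for illustration: P(X=x) = C(n₁,x)·C(n₂,t−x) / C(n₁+n₂,t), where t is the total number of hernias. The two-sided p sums all tables no more probable than the observed one. Start from 12/104 v 3/104 (p=0.029) and remove three suture patients:

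| Of the three removed, number who herniate | Suture v mesh | p |
|---|---|---|
| 0 | 12/101 v 3/104 | 0.016 |
| 1 | 11/101 v 3/104 | 0.027 |
| 2 | 10/101 v 3/104 | 0.047 |
| 3 | 9/101 v 3/104 | 0.079 |

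The conclusion at 0.05 changes only in the last row. If excluded patients had an assumed hernia risk of 35%, the chance that all three herniate is 0.35³ = 4%. At an assumed 50% it is 0.5³ = 12.5%.

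**4. Type I error under selective removal.** Assume a true rate of 12% in both arms, 104 per arm, and k patients with hernia risk r removed from one arm only. The remaining rate in that arm is (104 × 0.12 − k·r)/(104 − k). The last column is the chance that a two-sided z-test at 5% is significant.

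| k | r (assumed) | Remaining rate | Type I error |
|---|---|---|---|
| 2 | 25% to 50% | 11.8% to 11.3% | 5.0% to 5.3% |
| 5 | 35% | (12.48 − 1.75)/99 = 10.8% | about 5.8% |
| 10 | 35% | (12.48 − 3.5)/94 = 9.6% | 8.4% |
| 10 | 50% | (12.48 − 5)/94 = 8.0% | 15.4% |

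**5. Non-selective removal.** If equal shares leave both arms regardless of risk, only power changes. Two-sided power for 12% v 3% is 69.6% at 104 per arm. It becomes 68.7%, 67.3% or 64.9% if 2%, 5% or 10% of each arm is removed (assumed shares).

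**The case against.** The strongest defence is that the rule speaks of faulty enrolment, which is an earlier step than randomisation. The follow-up surgeon takes consent, the inclusion criterion concerns patients planned for reversal with sutured closure, and parastomal hernia is recorded as a preoperative item. On that reading the criterion is settled before the operation, and part of the rule covers patients who never reach randomisation. This stands as a plausible intention. It does not remove the conflict, because the text sets no such limit.

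Three stronger readings are tempting, and the documents do not support them.

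- **The unblinded operating surgeon decides ineligibility during surgery.** This is an inference. The article does not name who decides or when. The early opening of the envelope, the criterion tied to standard closure and the form completed after surgery make the route possible, not established.
- **Difficult mesh cases would be dropped and the mesh effect inflated.** The criterion refers to standard closure, not to difficulty in placing mesh. The operation description deals with technical difficulty separately, and failure to place mesh would be non-adherence, covered by the two planned analyses. A shift from 12/104 v 4/104 (p=0.066) to 12/104 v 2/102 (p=0.010) would need a misuse of the rule and both excluded patients to herniate. If neither does, 12/104 v 4/102 still gives p=0.066.
- **Two or three exclusions would typically change the result.** That holds only from a borderline start and in the worst case, as the tables show.

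Nor do the documents require a later opening of the envelope. Its timing is clearly stated and contradicts nothing. Recruitment began in March 2018, so a change now would split the trial into two procedures. Once all randomised patients are kept, it is largely unnecessary for this bias.

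**Conclusion.** The contradiction is real and lies in the current text. It decides who is counted in the primary analysis, so it should be settled before the data are unblinded. A full protocol or analysis plan may say more, but the article itself states two rules that cannot both be followed for a randomised patient.

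The size of the harm is unknown, because the documents give no expected number of ineligible patients and no decision procedure. With about 16 hernias, a few selective exclusions could move a borderline result in the extreme case. Small or non-selective exclusions would change little, and material inflation of type I error needed about ten selective removals from one arm under the assumed risks. The mechanism that the criterion does suggest, removal from the suture arm, would work against mesh and so would not favour a false claim of superiority.

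**What to change.** Amend the first item of the discontinuation section along these lines:

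> *Patients found ineligible before randomisation are not analysed and appear only in the flow chart. Every randomised patient remains in the intention-to-treat analysis in the allocated arm. A patient found ineligible after randomisation is left out only of the per-protocol or a sensitivity analysis. That decision is made blind to arm, from facts recorded before randomisation, and the number and reasons are reported by arm.*

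Add a cross-reference in the statistical methods section. The operation protocol cannot be the source for the decision, because it is completed after surgery by a surgeon who knows the arm. Pre-randomisation notes should be used instead.

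The cost is a change of wording, which can also be applied to patients already recruited. No sample size figure changes. The one downside is slight dilution of the effect by a few ineligible patients, and the per-protocol or sensitivity analysis will show it.

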#### Strategies to improve adherence to interventions

Patient adherence is expected to be good because the study follow-up will be done in conjunction with the routine cancer follow-up. The clinicians’ adherence will be continuously followed up with information and reminders.

#### Relevant concomitant care permitted or prohibited during the trial

All relevant concomitant care is permitted during the trial.

#### Provision for post-trial care

There will be no specific provisions for post-trial care. The patients will be treated according to established routines.

### Outcomes

#### Primary outcome

The primary outcome is a hernia at the former stoma site at any time point during the 3-year study follow-up. Hernia will be diagnosed through CT abdomen with and without strain, performed 1 and 3 years after cancer surgery. A patients’ questionnaire will be run at the same time.

#### Secondary outcome

The secondary outcomes are postoperative complications, length of stay, and operation time at the 30-day visit, assessed by clinical investigation, protocol, and questionnaire.

### Participant timeline

#### Entry procedures

Patients operated on for rectal cancer with low anterior resection with loop ileostomy will be screened for enrolment after rectal cancer surgery is performed and the patient is planned for loop ileostomy reversal.

